## **Outcomes: Assessment**

### *Visual attention (situation awareness)*

Will be conducted with the wearable eye tracker (Pupil Labs, Core Eye Tracker, Berlin, Germany. 160×51mm, high speed 120Hz and 200Hz, <https://pupil-labs.com/products/core>). This wearable eye-tracker is modular, easy to clean (disinfect), durable, lightweight, and ergonomically designed for safe use and deployment in any settings. It is fully mobile as it connects to a smartphone for data capture ensuring the wearer is free to move and their normal movement activity are not restricted. Data is wirelessly transferred to Pupil Labs proprietary software and stored locally. Data will then be stored on a secure server where further analysis of those data will be made using a custom-made MATLAB® (MathWorks Inc, Massachusetts, USA) algorithm

From all the simulation eye-tracking videos, the following will be analysed:

- i. Descriptors pertaining to AOI on: the baby, monitors (e.g., examining pulse oximeter), pressures on the T-piece resuscitation device (*neopuff*), mask technique, oxygen administration, endotracheal intubation (if applicable), performance of procedures like umbilical vein catheterisation, team members, and timer on the resuscitaire.
- ii. Time spent on each AOI (indicating VA distribution).
- iii. Three eye movements including fixations, saccades and smooth pursuits.

Analysis of eye tracking videos will be performed by the research team. However, one of the limitations of eye tracking is that it does not capture the situations of “Inattentional blindness”. Meaning the operator may be looking at some aspect without putting their mind to it. This will be studied by using having an additional camera in the room to gather more (situational) detail in context.

### *Video*

A stationery video camera (camcorder) will record the entire simulation from a fixed position. This will help with the wider and post study assessment by the research team of the primary and secondary objectives. Recording will commence immediately before and cease after the simulation(s). This may help support the assessment of situational impairments beyond the eye tracking video. For understanding the operator’s comprehension, interpretation, and interventions we will study the overall team performance and communication.

### *Team performance*

In real time, two investigators who are NLS instructors will independently assess each scenario for team performance. We will use validated modified neonatal resuscitation performance evaluation (NRPE) tool for assessment. This tool was originally developed based on the recommendations of Neonatal resuscitation programme, American Heart Association. NRPE provides categorical score (yes=1 and no/incomplete action=0) for each of the actions. It marks the performance under three domains: (i) appropriateness of decision making, (ii) technical skills and (iii) time taken to perform the appropriate resuscitative measures. It has seven sub domains: (i) preparation and initial steps, (ii) communication of heart rate, (iii) bag/mask ventilation, (iv) chest compressions, (v) intubation, (vi) medication administration and (vii) umbilical vessel catheterisation. Results from this tool have been shown to be valid and with high inter-rater reliability.

We have modified NRPE tool to match recommendations of Neonatal life support in the UK. Modifications would include use of two sets of inflation breaths, use of ventilation breaths and other minor modifications (Appendix 2). NLS, UK recommends two sets of 5 inflation breaths as compared to timed action as per NRP (30 seconds of Positive pressure ventilation) and recommends logical sequence of action followed by assessment. For these reasons, we have removed the domain for “time taken to perform the appropriate resuscitative measures”. This tool’s content validity is assured as the tool originally by expert neonatologist and modified by practising neonatologist [name]. Response process validity controlling for potential sources of error with administration will be minimised by using standardised simulation environment, using the same two simulation scenarios, and maintaining the similar team structure for all the simulations. We would calculate inter-rater reliability by two independent NLS instructors which would provide internal validity.

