## **Participants**

Neonatal staff from James Cook Hospital will be invited to participate between April 2022 and August 2022. Participants will not be stratified according to any variable (e.g., age, gender). All nursing and paediatric trainees need to complete Neonatal life support course every 2 years.

Inclusion criteria include:

1. For medical staff: must be paediatric trainee (any level) who has worked at least 6 months in neonatal intensive care settings.
2. For nurse practitioners: must be currently working in neonatal unit for at least 6 months or more.
3. For nursing staff: must be staff currently working in the neonatal unit.
4. Must have valid NLS certification (completed NLS within the last 3 years).
5. Must have participated or observed one neonatal simulation.
6. Must provide written informed consent.

Exclusion criteria include:

1. Not willing to wear eye tracking device.

**Team selection:** Communications will be via email to recruit interested participants (including nurses, nurse practitioners and doctors). Team selection will occur a few weeks prior to the simulation and will be randomly chosen by placing all written participant names in sealed envelopes and pulled from a ballot box. Teams will have an equal distribution of roles (nurse/tier-1/tier-2) making sure that each consists of:

- i. One neonatal nurse,
- ii. One tier-1 trainee (senior house officer working as tier-1 with 1-3 years paediatric training or advanced neonatal nurse practitioners working as tier-1) and
- iii. Two tier-2 trainees (senior doctors with  $\geq 3$  years of paediatric training or nurse practitioners working as tier-2).

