## **Study algorithm**

Each team will participate in two simulation scenarios (i) term and (ii) preterm. With 3 teams, there will be total of 6 simulation experiments. Each team will undergo one scenario with a team leader and another scenario without a team leader. The sequence in which each team is allocated with/without team leader would be alternating with each team. For example, if team #1 starts with team leader for their preterm scenario, team #2 would participate same preterm scenario without team leader. This will ensure that both scenarios have an equal number of scenarios with and without a team leader.

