## Sample size

In a previous study using eye tracking glasses examining VA during neonatal resuscitation, in which the operator acted both as an airway manager and team leader. In this study operator spent 35% (SD 8) of time focused on the infant. With the presence of dedicated resuscitation leader, to improve the VA on the infant to 55% with 80% power and alpha error of 0.05, we will need to conduct 6 scenarios with 3 samples in each group (equalling 18 participants).

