## Statistics

This is an exploratory study consisting of XXX groups. To the authors knowledge, there has yet to be a comprehensive analysis of VA with eye-tracking in neonatal simulations examining impact of a team lead with a checklist. However, there has been a pilot study using eye-tracking in neonatal resuscitation which used a dataset of 6 participant video-based eye-tracking recordings of 5mins duration. Therefore, our anticipated dataset size of 24 participants, will provide greater insight to examine VA behaviour differences and detect impact of a team lead with a standardised checklist. Data will be analysed in SPSS (v23, IBM) and R studio (R. RStudio, Boston, MA, USA). To conform to the exploratory nature of the work, descriptive statistics such as means, and ranges will be used here based on the number of participants stratified across 4 teams. Independent t-tests will further explore any observable differences. Those data will be complimented with simple plots. Anonymised data will be made available on reasonable request.

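### Team performance (NRPE) gives six run-level results in three within-team pairs, but the only stated analysis counts participants and uses independent t-tests

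*Protocol*

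**What the plan says.** Under Team performance, the NRPE is completed for each simulation run by two assessors: "In real time, two investigators who are NLS instructors will independently assess each scenario for team performance". The same section gives the second assessor one stated use, the calculation of inter-rater reliability.

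Under Study algorithm the number of runs is fixed, "With 3 teams, there will be total of 6 simulation experiments", and so is the pairing: "Each team will undergo one scenario with a team leader and another scenario without a team leader". Under Participants, a team has four members: one nurse, one tier-1 trainee and two tier-2 trainees.

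The Statistics section is the only description of the analysis, for any outcome. It refers to "our anticipated dataset size of 24 participants", says that "descriptive statistics such as means, and ranges will be used here based on the number of participants stratified across 4 teams", and continues: "Independent t-tests will further explore any observable differences". It calls the study exploratory. The Sample size section gives a different count: "we will need to conduct 6 scenarios with 3 samples in each group (equalling 18 participants". That calculation concerns visual attention on the infant. None is given for NRPE.

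**The concern.** A team score exists once per run, so the number of participants is not the amount of information available on it. The analysis text names no run-level or team-level unit, and its test treats the two conditions as coming from separate groups although every team supplies both.

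The participant basis cannot be set aside as applying to visual attention only. The Statistics section says the 24-participant dataset will also serve to detect the effect of a leader with a checklist. The Outcomes section describes the secondary outcomes, team performance and workload, in nearly the same terms.

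Team performance is the first secondary aim. At stake are a p-value that does not mean what it says, in one direction or the other, and a reported n of 18 or 24 where there are six results from three teams.

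**Working it through.** **The plan's own figures.** The one sample size calculation can be reproduced. For means of 35% and 55%, SD 8, 80% power and alpha 0.05 (taken as two-sided, since the protocol does not say), the normal formula gives n per group = 2 × (8 × (1.960 + 0.842) / 20)² = 2.51, rounded up to 3. That is 6 runs. The participant totals do not follow from it:

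- 18 = 6 runs × 3 records.
- 3 teams × 4 members = 12 people, and 12 people × 2 runs = 24 person-runs.
- 24 participants in the 4 teams of the Statistics section would be 6 per team, against the 4 under Participants.

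**What exists for NRPE.** 3 teams × 2 runs = 6 results, 3 with and 3 without a leader, in 3 pairs.

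**Reading A: participant rows.** Suppose each of the 3 + 3 run scores is entered k times. The difference in means is unchanged, the nominal degrees of freedom become 6k − 2 instead of 4, and the t statistic is multiplied by √((6k − 2)/4). With no leader effect, normal scores and independent runs, the true error rate is 2 × P(t on 4 df > c / √((6k − 2)/4)), where c is the critical value on 6k − 2 df.

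- k = 3 (18 rows): 16 df, multiplier √(16/4) = 2.00, error rate 34.9%.
- k = 4 (24 rows): 22 df, multiplier √(22/4) = 2.35, effective critical value 2.074 / 2.345 = 0.884, error rate 42.6%.

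**Reading B: one row per run.** With k = 1 the test has 4 df and an error rate of 5.0% if a team's two runs are uncorrelated. Positive correlation makes the unpaired standard error too large, so the test becomes conservative.

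**Effect of correlation.** The protocol gives no within-team correlation, so a range is assumed. Rejection rates of a nominal 5% two-sided test with no leader effect (exact for the unpaired tests at correlation 0, otherwise by simulation with 300,000 replicates):

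| Correlation between a team's two runs | 3 v 3 runs, unpaired | 3 rows per run | 4 rows per run | Paired, 3 differences |
|---|---|---|---|---|
| 0 | 5.0% | 34.9% | 42.6% | 5.0% |
| 0.25 | 3.4% | 29.0% | 36.6% | 5.0% |
| 0.5 | 2.1% | 22.0% | 29.1% | 5.0% |
| 0.75 | 1.0% | 12.8% | 18.1% | 5.0% |

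**Scenario.** These figures assume no difference between the term and preterm scenarios. With three alternating teams the leader runs split 2:1 by scenario. Adding a scenario shift of 1 to 2 SD at zero correlation moves the rates to 31.9% to 26.8% for three rows per run, 39.7% to 35.3% for four, and 3.9% to 1.9% for 3 v 3 runs.

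**What three pairs can show.** A paired t-test on three differences has 2 df and a critical value of 4.30. For 80% power the mean difference must be about 3.3 SDs of the differences.

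**The case against.** The strongest reply is that the protocol nowhere assigns a team's score to its members. In the Statistics section the participant count qualifies the means and ranges, which equal copying would not change. The t-test sentence names neither outcome nor unit. For a score given once per run, three against three is a natural reading, and it has no inflation. This stands. A reader might infer that the plan prescribes copied scores and so an error rate of 43%. The documents do not support that.

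A reader might likewise infer that both assessors' forms would be entered as separate observations, which would give 23.2% if the two agreed perfectly. The protocol mentions the second assessor's scores only for inter-rater reliability, so this has less support still.

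Nor can it be said flatly that the standard error would be less than half its proper size. The factor 2.35 holds for four rows per run at zero correlation. At correlation 0.5 it is 2.35 × √0.5 = 1.66, and it drops below 2 once the correlation exceeds about 0.27.

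It can also be argued that the unit of analysis and the rule for combining assessors belong in a statistical analysis plan, and that the study is exploratory. The combining rule alone could indeed wait. But the protocol is not silent: it states a basis and a test, and a later plan could analyse NRPE properly only by departing from both. The exploratory label limits the harm to misleading p-values and a misleading n. It does not make the method fit.

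Finally, within-team differences are not a clean leader effect. Each team has its leader in only one of its two scenarios, so each difference also contrasts term with preterm. The term scenario requires chest compression and umbilical epinephrine, which fall under NRPE sub-domains. This stands, and the fix allows for it.

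**Conclusion.** The point holds in conditional form. The documents settle that NRPE yields six run-level results in three within-team pairs, and that the only stated analysis rests on participants and independent t-tests. That analysis is wrong for this outcome on participant rows (about 13% to 43% false positives at a nominal 5%). On run scores it is miscalibrated the other way whenever a team's two runs are positively correlated (about 1% to 3% at correlations of 0.25 to 0.75, and 5% only at zero).

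These sizes rest on normal scores, no scenario effect, three or four rows per run, and assumed correlations from 0 to 0.75. Which reading the investigators intend cannot be told from the protocol. The correction is worth making because it is right under either.

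**What to change.** In the Team performance and Statistics sections:

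- State that the scenario run is the unit of analysis for NRPE.
- Average the two assessors' scores to one value per run, and keep both scores for inter-rater reliability.
- Report all six values and the three within-team differences (leader minus no leader) descriptively, each labelled by term or preterm scenario.
- Give n for team performance as 6 runs in 3 teams, not 18 or 24 participants.
- State that the independent t-test is not applied to NRPE.

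The team and participant counts in Study algorithm, Sample size and Statistics should be reconciled at the same time.

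The change is to wording only and needs no extra data. Its cost is that the team performance comparison becomes descriptive and its stated n falls to 6. Little is lost, since a paired test on three differences could detect only a very large effect.

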#### Secondary aims:

To examine impact of a team briefing prior to resuscitation on:

- 1) Team performance using the validated modified neonatal resuscitation performance evaluation (NRPE) tool, when (i) the operator is managing both airway and acting as team leader, compared to (ii) having a dedicated team leader with checklist.
- 2) Compare the workload with or without a team leader and standardised checklist. We will use National Aeronautics and Space Administration task load index (NASA-TLX) for assessing the workload.

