## **Simulation**

Prior to each simulation, participants will receive briefing about features of simulation dolls (i.e., to mimic the patient), how they need to assess the doll, and what information they need to obtain from the simulation instructors. Before each scenario each team will have approximately five minutes to prepare for the simulation. We will have two scenarios, one with management of an extreme preterm infant and another with the management of a term newborn with complications at delivery. Details of term and preterm resuscitation scenarios are provided in Appendix-1 and Appendix-2. Both these scenarios were used previously in our neonatal unit simulations. Both the simulation scenarios will need endotracheal intubation with the term baby scenario needing chest compression and umbilical vein administration of epinephrine. We will use the SimNewB (Laerdal Medical, Laerdal, Stavanger, Norway) low

HUFIN\_V5\_March 2022 IRAS: 314695 10

fidelity manikin for term and Premature infant Anne-low fidelity (Laerdal Medical, Laerdal, Stavanger, Norway) for the preterm scenarios, respectively. The two scenarios will be the same for all participants. We will run the two simulation scenarios with three different teams, giving a total of 6 scenarios. Each scenario will be running approximately for 10-15 minutes.

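### NRPE actions are scored 1 or 0 with no stated not-applicable option, so with three alternating teams summed scores would carry part of the term-preterm gap into the leader comparison

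*Protocol*

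**What the plan says.** **Scoring.** The Protocol's Team performance section gives a two-way rule: "NRPE provides categorical score (yes=1 and no/incomplete action=0) for each of the actions". It describes no code for an action that does not apply and no denominator. It then lists the content of the tool: "It has seven sub domains: (i) preparation and initial steps, (ii) communication of heart rate, (iii) bag/mask ventilation", followed by "iv) chest compressions, (v) intubation, (vi) medication administration and (vii) umbilical vessel catheterisation". The UK modifications are referred to Appendix 2, which is not available here.

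**Scenarios.** The Simulation section says: "Both the simulation scenarios will need endotracheal intubation with the term baby scenario needing chest compression and umbilical vein administration of epinephrine".

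**Comparison.** The first secondary aim sets the two arms of the team-performance comparison: "the operator is managing both airway and acting as team leader, compared to (ii) having a dedicated team leader with checklist".

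**Allocation.** The Study algorithm section gives each team one scenario with a leader and the other without, alternating from team to team. It says "With 3 teams, there will be total of 6 simulation experiments" and claims that each scenario will be run equally often with and without a leader.

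**Analysis.** The Statistics section plans descriptive summaries and independent t-tests, states no scenario term, and refers to four teams.

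**The concern.** The actions named for the term scenario map onto three NRPE sub-domains: chest compressions, medication administration and umbilical vessel catheterisation. If the 1/0 rule is applied as stated to every listed action and the items are added up, a preterm run has a lower ceiling than a term run, however well the team performs.

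A lower ceiling alone does not bias the leader comparison. Bias arises when one leader condition contains more preterm runs than the other, and three alternating teams force that. The estimated effect of a leader on team performance would then include a component that has nothing to do with the leader. Its direction would depend on which scenario received the leader twice. In a study that reports mainly descriptive means, a shifted mean difference is the result the reader takes away.

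**Working it through.** **The plan's own figure.** The protocol gives no calculation for NRPE. Its only calculated figure is the visual-attention sample size: 2 x [8 x (1.96 + 0.84)/20]^2 = 2.51, rounded up to 3 per group. This reproduces but does not bear on the present point.

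**Step 1: scenario split.** Three alternating teams, taking team 1 as having its leader in preterm (P) rather than term (T):

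| Team | With leader | Without leader |
|---|---|---|
| 1 | P | T |
| 2 | T | P |
| 3 | P | T |

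The leader condition has 2 P + 1 T and the other has 1 P + 2 T. Starting the other way reverses this. With an odd number of teams the claimed equality cannot occur. With four teams each condition has 2 P + 2 T.

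**Step 2: bias with no true leader effect.** Let q be the share of applicable items done (the same in every run) and f the share of all items that apply in preterm. On a 0-100 scale, term scores 100q and preterm 100qf, so the scenario gap is g = 100q(1 - f). The leader mean minus the no-leader mean is:

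- three teams: (2P + T)/3 - (P + 2T)/3 = (P - T)/3 = -g/3
- four teams: (2P + 2T)/4 - (2P + 2T)/4 = 0

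**Step 3: size.** Assume q = 0.80, with f varied because the item list is not available. The value f = 4/7 (57%) corresponds to equal item counts per sub-domain and none of the three sub-domains applying in preterm.

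| f | g | Bias with three teams (g/3) |
|---|---|---|
| 0.85 | 12.0 | 4.0 |
| 0.75 | 20.0 | 6.7 |
| 4/7 | 34.3 | 11.4 |

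The last row in full: preterm = 80 x 4/7 = 45.7; leader mean = (2 x 45.7 + 80)/3 = 57.1; no-leader mean = (45.7 + 2 x 80)/3 = 68.6; difference = -11.4. Varying q from 0.6 to 1.0 and the share not applicable from 0.2 to 0.5 gives 4.0 to 16.7 points.

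**Step 4: spread.** The within-condition SD from scenario alone is g/√3 with three teams and also with four. At f = 4/7 this is 34.3/√3 = 19.8 points.

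**Step 5: effect on the t-test.** With three per group and scenario as the only source of variation, the standard error is √(2 x (g²/3)/3) = 0.471g. So |t| = 0.333g/0.471g = 0.71 whatever the gap. That is nowhere near significance on 4 degrees of freedom: the gap inflates the denominator along with the difference.

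**Step 6: simulation.** Assumptions: 5 items per sub-domain, 80% performance, leader given to preterm twice, 20,000 runs.

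- No leader effect: the raw-total difference averages -4.0 of 35 items (-11.4 points). The t-test rejects in about 0% of runs.
- True leader benefit of 10 percentage points: the raw-total difference averages -1.5 items. The leader group scores higher in only 14% of runs, and the t-test again rejects in about 0%.
- Percentage of applicable items, same 10-point benefit: the leader group scores higher in 96% of runs. With no benefit, the expected difference is 0 and rejection is about 5%, with three or four teams.

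**The case against.** A reader might infer that a perfectly managed preterm run must score 0 on three of the seven sub-domains, so that NRPE totals simply measure which scenario was run. The documents do not support that:

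- The protocol never says that raw totals are the endpoint. The rule describes how an item is coded, and raw scores are specified only for NASA-TLX.
- The modified tool and the scenario scripts are in appendices that are not available. An applicability rule may already be there, or in an SAP.
- That preterm does not call for these actions is inferred from the contrast in the Simulation section. The Visual attention section lists umbilical vein catheterisation among the areas of interest without limiting it to term.
- The tool keeps a decision-making domain, under which correctly withholding an action might earn credit.
- At least four of the seven sub-domains are not singled out for the term scenario.
- The bias disappears with the four teams given under Statistics.

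All of this stands, and it makes the point conditional. What remains is that the protocol states a two-way item rule with no qualifier for applicability, although it names different actions for its two scenarios. It also claims a balance that its three-team design cannot give. The fact that the study is exploratory and the outcome secondary limits the weight of the point, but does not answer it.

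**Conclusion.** The point holds in conditional form. If actions that a scenario does not call for are scored 0 and summed, three alternating teams put one third of the scenario gap into the unadjusted leader comparison. At 80% performance that is about 4 to 11 points of 100 when 85% down to 57% of items apply in preterm. The 80%, the item counts and the use of a raw total are assumptions; the three teams and the alternation are in the protocol. With four teams the bias is zero and only the added spread remains.

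A reader might also infer a risk of false-positive findings. The calculations do not support this, since the raw-total test almost never rejects. The harm is a mean difference that can be shifted or reversed, and lost precision. This should be corrected before the first run.

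**What to change.** 1. Before the first run, mark on the NRPE score sheet which items apply to each scenario, following the scenario scripts. If the modified tool in the appendix already does this, say so in the Team performance section. Identify that appendix clearly, because the Simulation section also uses the label Appendix-2 for scenario details.
2. Define the team-performance score as the percentage of applicable items done, with non-applicable items left out of the denominator and not scored 0.
3. Compare leader with no leader with scenario as a factor, in place of the unadjusted independent t-test.
4. Reconcile the three-team and four-team counts, and correct the balance claim in the Study algorithm section if three teams are kept.

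**Cost.** A marked score sheet and a few sentences, with no extra data or staff. The scenario factor uses one degree of freedom (six runs: 4 residual degrees of freedom become 3). With three teams it also raises the variance of the leader effect slightly: averaging the two within-scenario comparisons gives σ²(1/2 + 1)/2 = 0.75σ², against 2σ²/3 = 0.667σ² unadjusted, a ratio of 1.125. That matters in an analysis this small, but it is a modest price for removing the artefact under either team count.
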